#### Missing data

All ROC analyses will include the participants that complete the diagnostic exam at 24 months. However, sensitivity analyses will be conducted where attrition-unrelated missing data will be replaced on a per analysis basis using multiple imputation algorithms. The proportion of missing data will be examined overall, by variable, by time point, and by treatment arm (if applicable). We will examine patterns of missingness through descriptive statistics and visual inspection, including the percentages and distribution of missing values and whether missingness is related to observed variables (eg, participant characteristics, previous assessments, or study site). These descriptions will be reviewed prior to any imputation. Based on the observed patterns, we will assess whether data are likely missing completely at random, missing at random (MAR) or missing not at random. Where missing data are judged to be attrition-unrelated and the MAR assumption appears plausible, multiple imputation by chained equations will be performed on a per-analysis basis. This approach makes the relatively mild assumption that missingness is related to observed data, an assumption often reasonable in longitudinal studies because the best predictor of a later outcome is typically its own prior measurement(s).^35^ To make the MAR assumption more plausible, auxiliary variables predictive of the variables with missing data and missingness itself will be included in the imputation model. Research shows multiple imputation assuming MAR performs well for ROC curve analyses, particularly for sample sizes >100.^36^

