### Study participants

A target sample of 696 infants will be recruited, with a final study sample size goal of n=600 completing study visits at 24 months of age. Inclusion and exclusion criteria by risk stratum are in table 1.

**Table 1 T1:** Participant inclusion and exclusion criteria

Risk stratum	Target sample	Recruitment location	Description	Exclusion criteria
Low	250	Local clinics	No concern for perinatal asphyxia	Preterm birth (<37 completed weeks’ gestation) Low birth weight (<2500 grams) Confirmed sepsis, meningitis, severe jaundice (ie, infants with bilirubin level exceeding 425 IU (25 mg%) or symptoms of acute bilirubin encephalopathy) Significant congenital malformation, genetic syndrome Congenital infection by serology, culture or consistent clinical findings Residence outside urban/peri-urban Harare Primary caregiver <18 years
Moderate	223	Local clinics Sally Mugabe Central Hospital postnatal ward NNU Prior study cohort*	Did not cry at birth Required resuscitation Thompson score remained <6^37 38^	
High	223	NNU Prior study cohort*	Experienced perinatal asphyxia Admitted to the NNU with neonatal encephalopathy (ie, Thompson score 6 or more at any point after birth) Survived to hospital discharge without a potentially confounding illness	

* A parallel study focused on the Helping Babies Breathe/Essential Newborn Care intervention followed a cohort of high-risk infants until 6 months of age. A subset of these infants was approached for participation in the ChiDO study.

NNU, neonatal unit.

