### Sample size estimates

Each tool’s ability to predict NDI (aims 1 and 2) will be assessed using sensitivity, specificity and area under the receiver operating characteristic (AUROC) curve. Based on Ugandan data,^30^ 1.3% of low-risk and 29% of high-risk infants are expected to have NDI—approximately three and 59 children, respectively. For medium-risk infants, local unpublished data suggest a 5% NDI rate, or about 10 children, constituting an overall incidence of 12%. Assuming about 15% loss to follow-up, the two-sided 95% CIs for 0.85 sensitivity, specificity and AUROC estimable from this study will be 0.75 to 0.92, 0.82 to 0.88 and 0.79 to 0.91, respectively (table 2). Keeping other parameters unchanged, if higher loss to follow-up leads to a smaller analytic sample, the 95% CIs estimable from this study will be wider.

**Table 2 T2:** Precision of point estimates for sensitivity, specificity and area under the ROC curve for n=600 (95% CIs)

Statistic	Estimate	CI	Estimate	CI	Estimate	CI
Sensitivity	0.75	0.64 to 0.86	0.85	0.76 to 0.93	0.95	0.87 to 0.99
Specificity	0.75	0.71 to 0.79	0.85	0.82 to 0.88	0.95	0.93 to 0.97
AUROC	0.75	0.68 to 0.82	0.85	0.79 to 0.91	0.95	0.92 to 0.99

AUROC, area under the receiver operating characteristic; CI, confidence interval.

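### ROC analyses use only children who complete the 24-month exam, and imputation leaves out attrition, so no stated analysis corrects accuracy for loss that depends on the test result

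*Protocol article*

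**What the plan says.** The Missing data section of the protocol article fixes the analysis set: "All ROC analyses will include the participants that complete the diagnostic exam at 24 months". It then offers a secondary step: "sensitivity analyses will be conducted where attrition-unrelated missing data will be replaced on a per analysis basis using multiple imputation algorithms". The limit is repeated with a further condition: "Where missing data are judged to be attrition-unrelated and the MAR assumption appears plausible, multiple imputation by chained equations will be performed". The term for gaps unrelated to attrition is not defined.

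The same section plans to tabulate missingness, to see whether it is associated with child characteristics, earlier assessments or site, and to judge the missingness mechanism before imputing. It defends imputation on the ground that earlier measurements of an outcome predict it best, and it promises auxiliary variables.

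Loss also appears in the design. The Study participants section gives the numbers: "A target sample of 696 infants will be recruited, with a final study sample size goal of n=600 completing study visits at 24 months". Under Sample size estimates, the precision figures are given "Assuming about 15% loss to follow-up", and that section says higher loss would widen the intervals. It does not mention bias.

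Two other sections bear on who returns. Setting and study population places most visits at municipal clinics but the final visit at the Children's Rehabilitation Unit (CRU). Referrals sends children with identified delays to the same unit.

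**The concern.** The 24-month diagnosis is the reference standard. A child who misses that exam has index test results but no verified outcome. The primary rule drops such children, and the only sensitivity analysis excludes attrition in terms. This is a restriction written into the text twice, not a detail left to a fuller plan.

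If attendance at 24 months is related to the index result, completers-only accuracy carries verification bias. The documents make this plausible: a child with poor early scores may already attend the CRU, while a well child must make a new journey there. Sensitivity and specificity then move in opposite directions. That affects the reported accuracy and the choice of cut-offs, which the Data analysis section sets out to make.

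The plan's own argument for imputation also supports using earlier scores for children lost before 24 months. Table 3 schedules MSEL and ASQ at 3, 6, 12 and 18 months alongside HINE and GSED, and MSEL is one component of the 24-month outcome.

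**Working it through.** **1. Expected loss.** 696 − 600 = 96 children, and 96/696 = 13.8%. At exactly 15%, 0.15 × 696 = 104. The two statements agree closely.

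**2. The plan's precision.** The stated case counts are 3 + 10 + 59 = 72 of 600 (12%), leaving 528 without NDI. At a true value of 0.85:
- Specificity: 1.96 × √(0.85 × 0.15/528) = 0.030, giving 0.82 to 0.88, as stated.
- Sensitivity (exact binomial): 0.746 to 0.923, against a stated 0.75 to 0.92.
- AUROC (Hanley–McNeil): 0.793 to 0.907, against a stated 0.79 to 0.91.

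The stated half-widths are thus about 3 points for specificity, 8.5 for sensitivity and 6 for AUROC.

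**3. Loss that depends on the index result.** Let rp and rn be retention among index-positive and index-negative children. Then
- observed sensitivity = Se·rp / [Se·rp + (1 − Se)·rn]
- observed specificity = Sp·rn / [Sp·rn + (1 − Sp)·rp]

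With Se = Sp = 0.85 and prevalence 12%, the index-positive share is 0.12 × 0.85 + 0.88 × 0.15 = 0.234. Overall retention is held at 0.86. The splits are assumptions, because the documents give none.
- rp = 0.95: rn = (0.86 − 0.234 × 0.95)/0.766 = 0.833. Sensitivity = 0.8075/(0.8075 + 0.1249) = 0.87. Specificity = 0.7076/(0.7076 + 0.1425) = 0.83.
- rp = 0.70: rn = (0.86 − 0.234 × 0.70)/0.766 = 0.909. Sensitivity = 0.595/(0.595 + 0.1363) = 0.81. Specificity = 0.7726/(0.7726 + 0.105) = 0.88.

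**4. Range at exactly 15% loss.** Here prevalence comes from the Table 1 targets: (250 × 0.013 + 223 × 0.05 + 223 × 0.29)/696 = 79.07/696 = 11.4%.

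| Loss, index-positive | Loss, index-negative | Sensitivity | Specificity |
|---|---|---|---|
| 5% | 18% | 0.868 | 0.830 |
| 15% | 15% | 0.850 | 0.850 |
| 25% | 12% | 0.828 | 0.869 |
| 40% | 7.6% | 0.786 | 0.897 |

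The last row is an extreme split, shown only to mark the edge.

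**5. AUROC.** In a binormal simulation of 400,000 children (true AUROC 0.85, overall loss 15%), the log-odds of loss ran from −1 to +1 per within-group SD of score. Completers-only AUROC was 0.842, 0.847, 0.850, 0.845 and 0.835, so the largest shift is 1.5 points. In that last run, sensitivity at a fixed cut-off fell from 0.85 to 0.794, so a stable AUROC does not protect the cut-off results.

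**6. Loss that depends on something else.**
- True NDI status only: the retention factor cancels, Se·r/[Se·r + (1 − Se)·r] = Se, and likewise for specificity. There is no bias.
- Risk stratum only, with equal accuracy across strata: no bias.
- Risk stratum only, with assumed unequal accuracy (sensitivity 0.60/0.70/0.90 and specificity 0.92/0.87/0.72 in low/moderate/high risk): across three uneven loss patterns, sensitivity moved from 0.859 to between 0.853 and 0.865, and specificity from 0.852 to between 0.844 and 0.859. All shifts are under 1 point.

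**7. Does correction work?** In the simulation, inverse-probability weighting gave AUROC 0.849–0.850 and sensitivity 0.849–0.850. The weights were the true retention probabilities, so this shows what is achievable when loss depends only on observed scores. It does not guarantee that result in practice.

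**The case against.** The strongest reply is that loss is not ignored. Recruitment is inflated, precision allows for it, missingness will be examined against earlier assessments, and Table 3 gives the 24-month visit a 180-day window. All of this stands. A reader might infer that attrition is never addressed, and the documents do not support that. What is absent is a corrective analysis to use if selective loss is found.

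A reader might also infer that any loss related to risk or severity biases the results. Step 6 shows otherwise: loss must track the index result within outcome groups, or accuracy must differ by stratum.

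The size is modest. AUROC hardly moves, and the sensitivity shifts in step 3 lie inside its interval. The one hint on direction, referral to the CRU, points towards better retention of index-positive children, which is the milder of the two scenarios in step 3. This stands and limits the weight of the point.

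Imputation has limits too. Formal hearing and vision tests and the diagnostic exam take place only at 24 months. Children who miss all of the 3-, 6- and 12-month visits are withdrawn and would have almost no scores. The documents do not say when loss occurs. These limits belong in the description of the added analysis. They do not justify omitting it, since a completers-only analysis needs loss to be unrelated to the index score given outcome.

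Finally, a reader might infer that deaths after discharge vanish from the analysis. That rests on silence in a condensed article which refers to a fuller protocol, so it is not a finding. A death-or-NDI endpoint would also change the target that the aims set.

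**Conclusion.** The point holds in a limited form. By its stated rules the plan has no analysis that corrects accuracy for loss before the 24-month exam, although 96 to 104 of 696 children are expected to be lost and earlier scores should exist for at least some of them. The undefined attrition term leaves it unclear whether a missed final visit without withdrawal could be imputed.

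If exam completion depends on the index result, the plausible shift is about 2–4 points in sensitivity and 2–3 points in specificity, in opposite directions. Only the specificity shift is comparable to its stated half-width. The AUROC shift is at most about 1.5 points. These sizes rest on assumed retention splits and a true value of 0.85 for each measure. With equal retention there is no shift. The point is worth correcting, but it does not undermine the design or the main AUROC results.

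**What to change.** Keep the completer analysis as primary. In the Missing data section, remove the restriction to gaps unrelated to attrition in both places. Add a sensitivity analysis, reported beside the completer result for every tool and age, that does one of the following:
- imputes missing 24-month NDI from risk stratum and the available earlier GMA, HINE, GSED, MSEL and ASQ scores; or
- weights completers by the inverse probability of completing the exam, modelled on the same variables.

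State that the analysis relies on MAR, that children with no earlier scores contribute little, and that the hearing, vision and clinical-diagnosis components of NDI have no direct prior measurement.

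The cost is a change of wording and one further set of runs on data already being collected, with no new visits. The downside is dependence on a MAR model and slightly wider confidence intervals in the added analysis.

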#### Data management

Data will be entered directly into a University of Zimbabwe (UZ) secure REDCap database and a UZ secure ODK server for GSED-related data or collected on paper forms and entered promptly by research staff. Only authorised research team members from University of California San Francisco (UCSF) and UZ will have access to both REDCap and ODK data. Digital videos for GMA assessment or QA videos will be labelled only by study ID number, visit age and date of collection. They will be stored on a secure cloud-based server accessible only to necessary research personnel. All study computers/tablets will be encrypted and password protected. No personal devices will be used with PHI. Paper records of data collection forms will be kept in double locked filing cabinets in locked office suites. Signed informed consent forms will be filed separately in a secure, locked location.

## Ethics and dissemination

Ethical approvals have been received from the UCSF Institutional Review Board (#21-34337), Sally Mugabe Central Hospital, Medical Research Council of Zimbabwe (MRCZ/A/2825), City of Harare, Research Council of Zimbabwe (RCZ Registration No. 05077) and the WHO Research Ethics Review Committee. We do not anticipate risks during this study, though it is possible caregivers may feel stress/concern if their child is not developing or growing well, or if they feel uncomfortable talking about their mental health, home environment, etc. Additionally, multiple study visits and the cumulative time for assessment may cause stress or time lost from work; we have included participant travel support and small refreshments at each visit.

### Referrals

If any concerns arise during data collection procedures, study staff will notify the local Principal Investigator, a neurodevelopmental paediatrician. Families will be informed of any clinical diagnoses or NDI. If medical conditions are detected in the infant, they will be referred to the local paediatric clinics. If developmental delays are identified, families will be referred to CRU services, such as occupational therapy, physiotherapy, speech therapy and family/caregiver support and counselling. CRU services are available at no cost to families.

### Significance and relevance

If shown to be valid, the GMA and HINE could be implemented in LMICs and provide much earlier, feasible and low-cost detection of children at elevated risk for NDI. They have the potential to markedly reduce the age at which children with or at risk for NDI are identified, allowing appropriate early intervention to be initiated by 6 months of age or earlier. Their potential for use by multiple levels of healthcare workers in LMICs can help to ensure that early detection occurs at both urban and rural health centres, promoting equity in access. Study findings will also contribute to international GSED validation efforts, including those for individual-level use of GSED, supporting improved neurodevelopmental assessment on a global scale. Specific to Zimbabwe, validation of these tools, along with use of the Washington Group/UNICEF Module on Child Functioning, will also support the goal of obtaining high quality data on NDI. Finally, validation in the proposed sample will set the stage for rapid evaluation, clinical use and research implementation with other at-risk groups (eg, in preterm infants, severe hyperbilirubinaemia or acute malnutrition).

## Conclusion

In Shona, the local language of Harare, Zimbabwe, chido translates to ‘something loved’. This study, the Child Development Observation Study—the ChiDO Study—aims to inform more widespread, feasible neurodevelopmental assessment in LMICs to ensure that every child and family has an opportunity to thrive and receive the resources they need.
